
### Data Collection Procedures

Data are collected by trained assessors following detailed standard operating procedures to ensure consistency across assessments. At the same time, a universal design approach [26] is taken to promote inclusion and accessibility for all children. For participants with identified disabilities, a member of the study team experienced in working with children with disabilities will consult with the classroom educator and the study team’s resource consultant in advance of the assessment to plan any necessary adaptations. While standardized procedures are followed whenever possible, assessments that a child does not have the ability to complete are not administered. In some cases, tasks may be modified to better align with a child’s abilities (eg, permitting use of a mobility aid when demonstrating a kicking task). All deviations from standard procedures are documented, and sensitivity analyses will be conducted to examine the impact of including or excluding children who did not complete the full standardized protocol on the study results.

Assessments with children take place on-site during ELCC hours 3 times per year: baseline (T0), 6-month follow-up (T1), and 12-month follow-up (T2). For children who reenroll in the study after 1 year, assessments will continue every 6 months for up to a total of 6 follow-up assessments. There will be 3 waves of data collection representing 3 cohort groups across 3 years (Figure 3). Important to note, “waves” are distinct from time points; time points (eg, T0 and T1) refer to when data are collected during the study, whereas waves refer to when groups of participants are enrolled in the study. Testing of all children is typically completed over a 1-month period in the summer (August) and winter (February). To support children’s understanding of the research activities and to promote their engagement, a Research Garden (Figure 4) was created at the experimental ELCC program. This space offers a welcoming, familiar environment where children can explore materials, ask questions, and participate in tasks more comfortably. By embedding the research within an inviting, playful setting, the Research Garden helps motivate children, reduce apprehension, and foster a sense of curiosity and involvement in the study. Although we were unable to establish a Research Garden at usual care sites, we support children’s engagement through regular visits to the center to build familiarity with the research team. We also worked with the educators to select a temporary, quiet, child-friendly space for assessments and will use the same space for future assessments to build comfort. We also use engaging materials (eg, a teddy bear wearing an accelerometer) and small incentives (eg, stickers) to promote participation.

**Figure 4. F4:**
[figure not shown]
Research garden at the experimental Early Learning and Child Care program.

Caregiver questionnaires are distributed via REDCap, a secure, institutional web-based data management platform, following each assessment and are completed within 7 days of the assessment date. Each child is assigned a unique study ID and added to a password-protected master list to securely track data across all time points. During each assessment, children complete a battery of standardized assessments appropriate to their age group and ability (details provided below). Data are recorded on hard-copy data collection forms and then entered into REDCap following the assessment. One research staff member enters the data, and another verifies it for accuracy.

Educator questionnaires are distributed following the same schedule as child assessments. Educators receive a REDCap questionnaire 3 times per year and are asked to complete the questionnaire electronically within 7 days of receiving it. Educators are also invited to reenroll in the study for up to 3 years (or a maximum of 6 follow-up questionnaires).

### Outcome Measures

The objectives of this study will be assessed using a combination of direct child assessments and caregiver and educator questionnaires. These instruments are described in detail in the following section. A summary of measures for children, caregivers, and educators can be found in Table 1.

**Table 1. T1:** Child, caregiver, and educator outcome variables and measures used in the SPROUT^a^ study.

Outcome and measure	Informant			
	Child	Caregiver	Educator	ELCC^b^ center
Child outcomes				
Physical development				
Motor skills				
PDMS-3^c^	✓			
Nine-Hole Peg Test	✓			
Supine Timed Up and Go	✓			
ASQ-3^d^		✓		
ECDI^e^		✓		
Upper limb strength				
Hand Grip Dynamometer	✓			
24-hour movement behaviors				
Accelerometer	✓			
Questionnaire		✓		
Social-emotional development				
Problem-solving				
ASQ-3		✓		
Social-emotional skills				
ASQ-3		✓		
ECDI		✓		
Cognitive development				
Executive functioning				
ECDI		✓		
Early Years Toolbox - [name], Go/No-Go	✓			
Caregiver outcomes				
Affective and instrumental attitudes toward outdoor play				
Modified beliefs about caregiver support of child’s physical activity questionnaire		✓		
Outdoor play supports behaviors				
Modified caregiver support of child’s physical activity questionnaire		✓		
Educator outcomes				
Affective and instrumental attitudes toward outdoor play				
Modified beliefs about caregiveral support of child physical activity questionnaire			✓	
Outdoor play knowledge and confidence				
Early Childhood Educators’ Confidence in Outdoor Movement, Physical Activity, Sedentary and Screen behaviors (ECE-COMPASS) Questionnaire			✓	
Health and well-being				
Copenhagen Psychosocial Questionnaire, third edition (COPSOQ-III)			✓	
Other				
Injury statistics				
Author-generated questionnaire				✓
Quality of ELCC outdoor space				
Seven Cs Early Childhood Education Center assessment score				✓

a SPROUT: Sending Preschoolers Outside.

b ELCC: Early Learning and Child Care.

c PDMS-3: Peabody Developmental Motor Skills assessment, 3rd edition.

d ASQ-3: Ages and Stages Questionnaire, third edition.

e ECDI: Early Childhood Developmental Index.

### Child Assessments (Objective 1)

#### Overview

Child assessments are conducted individually onsite at the participating ELCC center and take approximately 45‐60 minutes per participant to complete. Assessments are conducted by researchers who have completed formal training on all assessments, including training on how to administer the different assessments among children with physical, sensory and/or developmental disabilities.

#### Anthropometry

For children aged 10‐24 months, body length is measured using an infant measuring rod (Seca GmbH & Co KG). Children are placed supine with their head aligned with the headboard and feet aligned with the footboard, straightening as best as possible. Weight is measured using a digital scale (Seca GmbH & Co KG) designed to measure child weight while in the arms of an assessor and measured to the nearest 0.1 kg. The assessor holds the child in their arms to complete the weight measurement, subtracting the assessor’s weight from the total to determine the child’s weight. For children aged 24‐59 months, the child’s height and weight are measured using a medical-grade digital scale (Seca GmbH & Co KG) and stadiometer (Seca GmbH & Co KG). If a child is 24‐59 months but has a disability that impacts their ability to stand prone without assistance (eg, cerebral palsy), the assessors will follow the standard procedures for children aged 10‐24 months (described above) that do not require a child to maintain an upright standing position without assistance, to measure height and weight.

For all children, regardless of age or disability, height and length and weight are calculated with the child’s shoes removed, and children are asked to remove any heavy clothing (eg, sweatshirt). Two measurements for height are taken to the nearest 0.1 cm. If measures differ by more than 0.5 cm, a third measurement is taken. The average of the 2 closest measurements is retained. Body weight is measured to the nearest 0.1 kg twice. Measurements are repeated a third time if they differ by more than 0.25 kg and an average of the 2 closest measurements is retained.

#### Physical Activity

Physical activity is measured using Actigraph accelerometers (Ametris, GT3XP-BTLE). The GT3XP-BTLE activity monitor is a small (3.8 cm × 3.7 cm×1.8 cm) light (27 g) sensor with no external controls or feedback. The accelerometer is secured by a belt and worn across the right hip. In line with existing recommendations for measuring children’s physical activity in the early years [27], children wear the accelerometer for 7 consecutive days (including during sleep), only removing it for prolonged water activities (eg, bathing and swimming). Caregivers are asked to keep a log of when the accelerometer is put on and taken off. To encourage compliance, the assessor explains to each child that the monitor is their “special belt” that measures their playing, resting, and sleeping, and the child is invited to choose a sticker to personalize their belt to take home. Physical activity data are analyzed using ActiLife software (version 6.15.0; ActiGraph) and R (version 4.4.2; R Core Team) [28] using RStudio version 2024.12.0+467 (Posit PBC) [29]. Data are downloaded in ActiLife using 15-second epoch lengths. Fifteen-second epoch lengths were chosen due to the short, sporadic activity bursts that are typical in young children [27]. Physical activity data are then processed and analyzed in RStudio. The *PhysicalActivity* package [30] is used to derive activity metrics from raw accelerometer data, including intensity classifications and summary variables. The *PhysActBedRest* package [31] supports the identification of sustained bedrest and waking periods to refine nonwear and rest interval detection. The *actigraph.sleepr* package [32] is used to score sleep and wake episodes based on ActiGraph accelerometer files, enabling the extraction of standardized sleep parameters. The Trost et al [33] and Pate et al [34] cut-points are used to determine minutes of light, moderate, and vigorous activity among toddlers (10‐35 months) and preschoolers (36‐48 months), respectively. The Tracy cut-points are used to determine hours slept [35]. If available, disability-specific cut-points will be used on a case-by-case basis for children with identified disabilities [36].

#### Motor Development

The Peabody Developmental Motor Skills assessment, 3rd edition (PDMS-3, Pearson Scientific) is used to measure children’s fine and gross motor skills. The PDMS-3 is designed to measure both fine and gross motor skills of children of various abilities from birth up to 6 years of age. The test is administered in-person by a trained researcher and takes between 30 and 45 minutes to complete depending on the child’s age and ability level. The PDMS-3 includes 5 core subtests, with 3 gross motor (body control, body transport, and object control) and 2 fine motor tests (hand manipulation and eye-hand coordination). A score is given based on the sum of each subtest. The PDMS-3 also produces a composite index score for gross and fine motor skills as well as a total score. The PDMS-3 has been previously established as a valid and reliable measure of motor skills in children with and those without disabilities aged 2‐4 years old [37].

The Nine-Hole Peg Test is used as a secondary measure of fine motor skills. The Nine-Hole Peg Test is completed by children aged 36 months and older in this study. The Nine-Hole Peg Test is part of the National Institutes of Health (NIH) toolbox [38] and is a widely used, reliable measure of manual dexterity in children with and those without disabilities [39,40]. The Nine-Hole Peg Test has also been shown to be a reliable measure of manual dexterity among children and youth with cerebral palsy [41].

The Supine Timed Up and Go (S-TUG) task is used as a secondary measure of gross motor skills, specifically a child’s motor coordination. The S-TUG task is completed by children aged 36 months and older in this study. S-TUG is considered a reliable measure of motor competence in children with high concurrent validity, interrater reliability, and intrarater reliability >0.80 [42]. Evidence also shows that the S-TUG tasks are highly reliable among children with cerebral palsy [43] and therefore by extension, may be accessible to children with similar physical disabilities.

A hand grip dynamometer is used to measure grip strength, an indicator of upper limb strength. The assessment is completed by children aged 36 months and older in this study. This assessment is also included as part of the NIH toolbox [38] and has been established as a valid, reliable, and feasible tool to measure upper limb strength in preschool-aged children, with an interclass correlation coefficient varying from 0.84 to 0.98 (intrarater) and from 0.81 to 0.96 (interrater).

#### Executive Functioning

Two tasks from the NIH Early Years Toolbox are used to assess visual-spatial working memory ([name]) and task inhibition (Go/No-Go). These tasks were developed as brief, playful assessments administered using an iPad to examine young children’s cognitive development. The [name] task assesses visual-spatial working memory. The Go/No-Go tasks assess a child’s inhibition. For more information on these assessments, see Early Years Toolbox [44]. These assessments have been previously validated in children aged 2.5‐5 years old and demonstrate very good reliability, convergent validity, and sensitivity [45,46]. Executive functioning tasks are completed by children aged 36 months and older in this study.

### Caregiver Questionnaire (Objective 1 and 2)

#### Overview

Caregivers complete an online questionnaire via REDCap (also made available in hard-copy format upon request) that has them report on family demographic characteristics, the child’s 24-hour movement behaviors (physical activity, sedentary behavior, and sleep), the home environment, aspects of the child’s development, and caregivers’ attitudes and behaviors toward active outdoor play. Each component of the questionnaire is briefly described below; for full details, refer to Multimedia Appendix 1.

#### Family Demographic Information

Demographic information of the caregiver and child collected includes caregiver age, sex, and gender; child age, sex, and gender; household income; and the outdoor environment at home.

#### 24-Hour Movement Behaviors and Outdoor Play

Items from the Canadian Health Measures Survey [47] are used to collect information on the child’s movement behaviors. Caregivers are also asked to report on the number of minutes their child spends outside playing on weekdays and weekend days.

#### Child Development

Child development is measured using 2 assessment tools completed by caregivers: the Early Childhood Developmental Index (ECDI) and the Ages and Stages Questionnaire, third edition (ASQ-3). The ECDI was developed by the United Nations Children’s Fund (UNICEF) to assess key child developmental milestones of children aged 24 to 59 months. The ECDI consists of 20 questions completed by a caregiver who asks them about the way their child behaves in different situations as well as their child’s skills and knowledge [48]. The ASQ-3 is a widely used screening tool for tracking and monitoring developmental progress among children aged 1 to 66 months that is completed by the caregiver [49]. The ASQ-3 measures development across 5 domains: communication, gross motor, fine motor, problem-solving, and personal-social, and has shown high validity and reliability [50].

#### Caregiver Attitudes and Behaviors Toward Outdoor Learning

Caregivers’ affective and instrumental attitudes and their current support behaviors toward outdoor play are measured using 6 items adapted from the caregiver support measure described by Rhodes et al [51] for school-aged children’s physical activity. Five items, also adapted from the caregiver support measure described by Rhodes et al [51], are used to measure caregivers’ current levels of support behaviors for outdoor play.

### Educator Questionnaire (Objective 2)

Each component of the educator questionnaire is briefly described below; for full details, refer to Multimedia Appendix 2.

#### Educator Health and Well-Being

Educator health and well-being are assessed using items from the Copenhagen Psychosocial Questionnaire, third edition. The Copenhagen Psychosocial Questionnaire, third edition, is an international research instrument designed for assessing and improving psychological conditions in the workplace [52]. International results showed acceptable to good reliability (Cronbach α >0.7) [52]. For the purpose of this study, we use items from the Job Satisfaction and Health and Wellbeing Scale.

#### Educator Knowledge and Confidence Toward Active and Outdoor Play

Educator knowledge and confidence toward outdoor play in ELCC are measured using the Early Childhood Educators’ Confidence in Outdoor Movement, Physical Activity, Sedentary and Screen behaviors Questionnaire. The Confidence in Outdoor Movement, Physical Activity, Sedentary and Screen Behaviors Questionnaire is a valid and reliable tool (test-retest statistics >0.62) that assesses educators’ task and barrier self-efficacy toward active outdoor play [53].

#### Educator Attitudes Toward Outdoor Play

Educators’ affective and instrumental attitudes toward active outdoor play are measured using items adapted from Rhodes et al [51] study exploring caregiver support for school-aged children’s physical activity. Six items are used to measure educators’ affective and instrumental attitudes toward supporting children’s outdoor play.

### ELCC Environment

#### Evaluation of the Outdoor Space

The Seven Cs framework [54] is used to assess the quality of the outdoor space at participating ELCC centers, using a checklist adapted for the following 7 criteria: character, context, connectivity, change, chance, clarity, and challenge. Two members of the research team visited each participating center to complete the checklist and achieve consensus on an overall quality score prior to the start of the study. The checklist took approximately 15 minutes to complete.

#### Injury Rates Within ELCC Programs

As part of this research study, we are also collecting child injury data to compare injury rates in outdoor-based versus conventional ELCC programs. These data are provided by participating ELCC programs and consist of a list of deidentified reported injuries (Multimedia Appendix 3).

### SPROUT-able Substudy (Objective 3)

As part of the SPROUT study, a substudy titled “SPROUT-able” is being conducted to assess social and built environmental barriers and facilitators to outdoor play and learning in natural spaces of the outdoor-focused ELCC program (experimental site) for children with disabilities and/or identified challenges in one or more functional domains (ie, seeing, hearing, walking, fine motor, communication, learning, and playing, behavior) [55].

### Community Engagement in SPROUT-able

To support meaningful community engagement in the SPROUT-able substudy, we formed a collaborative group of community partners and individuals invested in improving outdoor play opportunities for children with disabilities who have professional and/or lived experience with disability (which includes the children they work with, their own children, or themselves). These partners contribute lived and professional expertise to guide the substudy’s design and implementation. To clarify roles and support shared decision-making, we use the Involvement Matrix (Multimedia Appendix 4) [56]. The Involvement Matrix is a tool used in partner-engaged research to clarify and visualize the different roles and levels of participation that partners or stakeholders can take throughout the various phases of a research project. This approach promotes transparency, supports reciprocal learning, and ensures the research remains responsive to community priorities.

### Determining Disability Status

To identify children with a disability or who may potentially have a disability, we will use a combination of caregiver-reported diagnosis, a validated caregiver questionnaire of functional abilities, and reports from the inclusion support worker. As part of the SPROUT study caregiver questionnaire described previously, caregivers are asked whether their child has been diagnosed with a disability (yes, no, in the process of getting a diagnosis), and if yes, to provide a brief description. Recognizing that many disabilities go undiagnosed in early childhood [55], we have implemented 2 other processes for identifying children who may have additional challenges in one or more developmental domains that could impact their participation in outdoor play. First, all caregivers complete the Washington Group/UNICEF Child Functioning Modules - Ages 2‐4 Years [55]. This tool is designed to capture challenges a child experiences in daily functioning. Aligned with the International Classification of Functioning conceptual model of disability [57], this tool focuses on what children can do and the level of difficulty they experience, rather than on medical diagnoses. Questions cover 8 functional domains (ie, seeing, hearing, walking, fine motor, communication, learning, playing, and controlling behavior) with response options that capture different levels of difficulty to reflect the severity of a child’s functioning (eg, no difficulty, some difficulty, a lot of difficulty, and cannot do at all). For the purpose of the SPROUT-able study, children are identified as potentially having a disability if the caregiver indicates “a lot of difficulty” or “cannot do at all” in one or more functional domains, consistent with the Washington Group/UNICEF guidelines. Where appropriate, we will further categorize children by severity level (eg, low to high functional difficulty). Finally, the inclusion support worker, who works in collaboration with the study team and the ELCC center, will document which children require ongoing additional support in the classroom, indicating a potential disability or developmental challenge. The inclusion disability support worker will do this by completing a checklist that aligns with the Washington Group/UNICEF guidelines used in the caregiver questionnaire. Disability status is reassessed every 6 months, given the rapid developmental changes in early childhood and the evolving demands placed on children as they grow.

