### Participants and Settings

Caregiver-child dyads are eligible to participate if children are between the ages of 10‐59 months at baseline, attend a participating ELCC center for 6 or more hours per day, 3 or more days per week, and if the caregiver can read, write, and understand English and/or French. Children with and those without disabilities will be eligible to participate in this study and efforts will be made to ensure study procedures and instruments fit the needs and abilities of children with disabilities. Educators are eligible if they are currently employed at a participating ELCC center, and they can read, write, and understand English and/or French. Participants are recruited from 2 types of ELCC programs: outdoor-focused (experimental) and conventional programs (usual care). The experimental and usual care programs are both governed by the same childcare organization and are licensed under the same provincial regulations. Given this, the centers are comparable in terms of cost per day, staffing ratios, and mealtime and nap protocols. The main difference between the centers lies in how the centers deliver the early years curriculum and where programming takes place. Details of the experimental and conventional centers’ programs, including setting, curriculum, and time outside, are detailed below.

The outdoor-focused ELCC center serves as the experimental group. This center prioritizes extended outdoor play and learning, with children spending the majority of the day outside year-round, regardless of the weather. The center is situated on 500 acres of forested land that children explore daily for learning and play. This expansive natural environment features a thick canopy of tall, established trees that provide significant shade, as well as a rich and diverse landscape with largely natural, grassy ground cover. Tree species are well mixed and include native varieties such as sugar maples, oaks, and several coniferous species. The terrain is varied, with exposed roots, rocky sections, and small but steep elevation changes, alongside wetlands and visible rock deposits that contribute to the site’s natural character and afford diverse sensory and physical experiences.

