**Figure 2. F2:**
[figure not shown]
Images of the outdoor space at the outdoor-focused Early Learning and Child Care program (ie, experimental site).

Three conventional ELCC centers will serve as the usual care control group. These centers provide conventional programming with scheduled outdoor time typically meeting the regulated amount of outdoor time, a minimum of 2 hours a day (eg, 60 minutes, twice daily) in defined play areas (eg, playground, fenced-in grass, and fenced-in pavement or rubber spaces; Figure 3). Programming follows more structured routines with educator-led activities, guided by the same provincial early learning framework that the experimental site follows [23]. Physical environments include standard play materials and fixed playground equipment. The 3 conventional ELCC centers are located in different settings, one in an urban area inside an apartment building and is licensed for 49 children (10 infants, 15 toddlers, and 24 preschoolers). One is located in an urban area in the basement of a church and is licensed for 39 children (15 toddlers and 24 preschoolers), and one is in a suburban neighborhood attached to an elementary school and is licensed for 31 children (15 toddlers and 16 preschoolers); this site also has a kindergarten and school-age program. All locations (including the experimental location) are part of the Canada-wide ELCC program, which in Ontario in 2026 means that the childcare fee is capped at CAD $22.00 (US $15.50) per day.

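### The ages 2-4 functioning module and its one-domain cutoff are applied to every child from 10 months, so a typically developing infant could be flagged and counted in SPROUT-able.

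*Protocol article*

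**What the plan says.** Under Participants and Settings, dyads are eligible if "children are between the ages of 10‐59 months at baseline". Under Determining Disability Status, "all caregivers complete the Washington Group/UNICEF Child Functioning Modules", in the version whose title restricts it to children of 2 to 4 years. That section describes the content as follows: "Questions cover 8 functional domains (ie, seeing, hearing, walking, fine motor, communication, learning, playing, and controlling behavior". It then sets a cutoff, expressly for SPROUT-able. The label attached to a child who meets it is that of potentially having a disability, and the caregiver answer that triggers it is "a lot of difficulty” or “cannot do at all” in one or more functional domains".

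Two other routes stand beside the module: a caregiver-reported diagnosis, and a report by the inclusion support worker of children who need ongoing extra support. The support worker does this by "completing a checklist that aligns with the Washington Group/UNICEF guidelines used in the caregiver questionnaire". Status is reassessed every 6 months.

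Other instruments in the article carry an age band. The ECDI is given for 24 to 59 months, and the peg test, S-TUG, grip strength and executive function tasks are used only from 36 months. The disability section gives no such limit for the functioning module.

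**The concern.** The instrument's title gives it a floor of 2 years, and the study enrols children 14 months younger than that. In infancy, not walking and not speaking are ordinary developmental states. A caregiver of a 10-month-old who does not yet walk could truthfully choose the most severe answer for walking, and one such answer is enough. The flag would then record age, not functional difficulty, and would tend to disappear as the child matures.

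At stake is the composition of SPROUT-able. The flag is one route into that substudy, whose caregivers are given priority for interviews, and it may bear on who counts as having a disability in the comparison of GoPro recordings. A few infants admitted by age alone would matter in a group of 19.

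**Working it through.** **Inputs.** Table 2, age at baseline: experimental mean 28.4, SD 12.0, n = 54; usual care mean 32.4, SD 6.9, n = 32; all children 29.8 (10.9), N = 86. Results section: 19 SPROUT-able children, of whom 4 have a diagnosis, 3 have caregiver-reported functional difficulties and 12 were identified by the support worker.

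**Reproducing the article's figures.** Weighted mean age = (54 × 28.4 + 32 × 32.4)/86 = 29.9, with combined SD 10.5, against 29.8 (10.9) stated. With 23 usual care children, the number with a disability answer in Table 2, the result is 29.6 (10.8). The group ages are consistent with the overall row to within rounding and missing data. Also 4 + 3 + 12 = 19, so each child is counted once.

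**Children outside the module's age band.** Table 2 does not give the shape of the age distribution, so several were assumed.

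Plain normal, experimental group:
- Under 24 months: Φ((24 − 28.4)/12.0) = Φ(−0.367) = 0.357; × 54 = 19.3.
- Under 15 months: Φ((15 − 28.4)/12.0) = Φ(−1.117) = 0.132; × 54 = 7.1.

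Same normal cut at the entry age, with Φ((10 − 28.4)/12.0) = 0.063:
- Under 24 months: (0.357 − 0.063)/(1 − 0.063) = 0.314; × 54 = 17.0.
- Under 15 months: (0.132 − 0.063)/(1 − 0.063) = 0.074; × 54 = 4.0.

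Shapes matched to the stated mean and SD:

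| Shape | Under 24 months, of 54 | Under 15 months, of 54 |
|---|---|---|
| Truncated normal, 10-60 months | 22.5 | 7.7 |
| Beta, 10-60 months | 22.7 | 7.9 |
| Gamma | 21.8 | 6.0 |

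The ranges are therefore about 17-23 of 54 (31-42%) under 24 months and about 4-8 under 15 months.

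For usual care, the plain normal gives Φ((24 − 32.4)/6.9) = Φ(−1.217) = 0.112; × 32 = 3.6. The other shapes give 3.3-3.7. Some usual care rows in Table 2 do not add to 32 (sex 22, disability 23), so this count is less secure. Licensing points the same way: the church-basement center is "licensed for 39 children (15 toddlers and 24 preschoolers" and has no infant places, nor has the suburban center. Only the apartment-building center has any (10 of 49).

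**What has been observed.** Three of 19 SPROUT-able children are listed under caregiver-reported functional difficulty, so at most 3/19 = 16% could owe their place to the module alone. Their ages are not given. A child who entered at 10 months in August 2024 would be about 22 months old by August 2025, so this snapshot says little about flags at the first visits, which are not reported.

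**The case against.** The other side has real force on reach and size.

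- *Label.* The child is marked as potentially having a disability, formal diagnosis is a separate route, and reassessment every 6 months could clear a flag due only to immaturity. This stands as mitigation, but a later correction does not prevent the wrong flag at the visit where it is set.
- *Item wording.* The full caregiver questionnaire is in a multimedia appendix that is not shown. Its items might be age-referenced or branch by age, so the most that can be said is that a typical infant could meet the rule. The article's own statement nevertheless covers all caregivers without exception.
- *Numbers.* The non-walking or non-speaking mechanism concerns the youngest children. Nothing in the article shows that typical children of 15-23 months would reach the cutoff, so 17-23 measures use outside the age band, not error.
- *Support-worker checklist.* It follows the same guidelines, so a reader might suspect the 12 children identified that way too. That route is tied to ongoing need for additional support, and the children's ages are not given. The documents do not show the error there.

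A reader might also infer that the flag biases the comparison between groups, because the experimental sample is younger. The documents do not support this. The cutoff is stated for SPROUT-able, which runs only at the experimental site and has no usual care arm. The Data Analysis Plan lists disability status among example covariates without tying it to the module. The disability rows in Table 2 (yes, no, unsure, prefer not to answer) look like a direct caregiver answer. Child age is a listed covariate as well, which would lessen any effect.

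**Conclusion.** The concern holds as a defect in the rule for SPROUT-able classification. The text applies a module titled for ages 2-4 years, and its one-domain cutoff, to children from 10 months without any adjustment. Exposure at baseline is roughly 17-23 of 54 experimental children, with about 4-8 under 15 months, where a false flag is most plausible. These counts rest on an assumed age distribution around the Table 2 mean and SD. Misclassification in the August 2025 snapshot is at most 3 of 19 and may be zero; none has been demonstrated. An effect on the primary models is conditional on their disability covariate using this flag, and the article does not say that it does.

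**What to change.** Apply the module and its cutoff only at visits when the child is 24 months or older. Below 24 months, code module status as not assessed, and keep caregiver-reported diagnosis and the support worker's report of ongoing additional support as routes into SPROUT-able. Falling back on diagnosis alone would be wrong, because the article added other routes on the ground that many early disabilities are undiagnosed. Re-derive the Wave 1 flags on this rule, and keep module-only flags from under 24 months out of the disability covariate.

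This is a change to a derivation rule and needs no new data. The small cost is that some true early functional difficulties will be identified later. Module status will also be unavailable at baseline for about a third or more of the experimental children, against roughly a tenth in usual care, so not assessed must not be read as no difficulty.
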